### Data analysis

Data analysis will be conducted using IBM SPSS® Version 22. Results for each cohort will be analysed separately, although secondary data analysis will be conducted on all groups together. Interim analysis is planned with involvement from a patient and public involvement panel. Outcomes will be summarised at baseline, 7 days postoperatively, and 13 weeks postoperatively. The data analysis of the primary research question will include the following models:
Unadjusted model with PROMIS at 13 weeks as the outcome of interest, and the secondary outcome as the covariate of interest (i.e. change in BATT, handgrip strength and/or gait speed from baseline to 7 days).Adjusted model with PROMIS at 13 weeks as the outcome of interest, and the secondary outcome as the covariate of interest (i.e. change in BATT, handgrip strength and/or gait speed from baseline to 7 days), with adjustment for the baseline PROMIS score, and patient demographics (e.g. age, gender).Model with PROMIS at 13 weeks as the outcome of interest, with adjustment for baseline PROMIS, and all secondary outcomes as covariates to establish the strength of association between those secondary outcomes and the primary outcome. This model will be used to establish which of the secondary outcomes (i.e. change in BATT, handgrip strength and/or gait speed from baseline to 7 days) is most strongly associated with change in PROMIS at 13 weeks.

Change in PROMIS rather than change in SPPB, which can be considered an objective measure of physical function, has been selected as our primary outcome for two reasons. Firstly, our patient and public involvement panel considered their own perception of their physical function to be most important. Although perception of function may differ from objective function, how function is perceived for them as individuals was considered more important. Secondly, it will only be possible to obtain true pre-hospitalisation measures of SPPB for the elective cohort. PROMIS provides a method of evaluating physical function prior to admission in the emergency cohorts. Change in SPPB will be evaluated as a secondary outcome in the elective cohort.

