### Acute sarcopenia

Sarcopenia will be defined as per EWGSOP2 as handgrip strength below 16 kg in women or below 27 kg in men [2, 55], in combination with low muscle quantity or quality. Cut-offs for low muscle quantity and quality will be evaluated comparing the cohort against reference data in healthy young adults; cut-offs for BATT of 3.85 cm in women and 5.44 cm in men have been proposed [11]. Severe sarcopenia will be defined as additional presence of low physical performance; gait speed 0.8 m/s or less [56] or SPPB of 8 or less [57]. Acute sarcopenia will be defined as incident sarcopenia compared to baseline measurements at recruitment. The prevalence of sarcopenia will be calculated at each visit.

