## Discussion

This study will fully characterise changes in muscle quantity and function in a clinical setting and will provide invaluable information to researchers, clinicians, and patients. The results of this study have potential to lead on directly to further interventional studies to counteract these changes, with particular focus on identified mechanistic associations and clinical factors to guide risk stratification. The results may also lead to direct changes in clinical practice, including the embedding of our research tools into clinical practice, and changes in policy, such as promoting early mobilisation. Providing patients and members of the public with increased knowledge on their risk of declines in muscle quantity and function, and what this is likely to mean for them, can help to empower them in their own decision making and engagement with treatment and therapy.

We recognise that there are a number of limitations of our study. Firstly, this is a single site study, and therefore, the results may not be generalisable to the wider population. Secondly, the cohorts we have included are disease-specific. However, we consider that our results will provide proof of concept, which can be used to guide further research to increase understanding in other disease populations. As described, our study has been powered to detect within group differences in the minimally clinical important differences as derived from other studies. However, this has not been powered separately for gender and other covariates (e.g. cancer vs. not), which may affect measurements. Interim analysis has been planned and our patient and public involvement panel will be involved in the interpretation of these results. At this stage, we will review the overall progress of the study and consider if protocol amendments may be necessary.

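### Model 3, which ranks the muscle measures, drops Model 2's age and gender adjustment, and no model includes the starting value of BATT, grip or gait speed, so the ranking can be confounded

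*Protocol article*

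**What the plan says.** The Data analysis section of the protocol article writes out the covariates model by model.

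- **Model 1** is crude: "Unadjusted model with PROMIS at 13 weeks as the outcome of interest", with one muscle measure as covariate.
- **Model 2** keeps that outcome and covariate, "with adjustment for the baseline PROMIS score, and patient demographics (e.g. age, gender" being the examples given.
- **Model 3** enters the measures together, "with adjustment for baseline PROMIS, and all secondary outcomes as covariates to establish the strength of association between those secondary outcomes and the primary outcome". Demographics are not named.

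Model 3 has the deciding role: "This model will be used to establish which of the secondary outcomes" is most closely tied to change in PROMIS. In every model the muscle exposure is "change in BATT, handgrip strength and/or gait speed from baseline to 7 days", that is, an absolute difference in cm, kg or m/s. No model names the starting level of any of the three measures.

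Two other places bear on this. The Acute sarcopenia section uses sex-specific thresholds: "cut-offs for BATT of 3.85 cm in women and 5.44 cm in men have been proposed", and 16 kg against 27 kg for grip. The Discussion says of the sample size that "this has not been powered separately for gender and other covariates (e.g. cancer vs. not), which may affect measurements".

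**The concern.** The model that produces the study's ranking is less adjusted than the one listed just before it, and no reason is given. An absolute change score is often related to the level it starts from. Someone with a thicker thigh can lose more centimetres, and measurement error in the baseline reading enters the change with the opposite sign. If starting muscle, age or sex also predicts 13-week function over and above baseline PROMIS, leaving them out mixes the effect of losing muscle with the effect of having had more of it.

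Those two effects would be expected to oppose each other: more starting muscle goes with larger losses and with better function. The coefficient for loss would then be pulled towards zero. The pull need not be equal for BATT, grip and gait speed, so the order of the measures could change as well as their size. The article's Discussion wants the results to guide risk stratification, so the ranking is one of the study's main products.

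**Working it through.** The plan gives no figure for these models, so there is none to reproduce. The check has three parts.

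**1. Covariates side by side**

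| Model | Baseline PROMIS | Age, gender | Muscle change | Starting muscle value |
|---|---|---|---|---|
| 1 | no (crude by design) | no | one measure | no |
| 2 | yes | yes | one measure or more | no |
| 3 (ranks the measures) | yes | not named | all | no |

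**2. How much the omission could matter (BATT only)**

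From the article: BATT mean 3.6 cm and SD 1.1 cm (Power calculation). The pilot loss is 0.76 cm, and 0.76/3.6 = 21% of the mean.

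Assumed, not in the article: true slope 3 PROMIS points per cm of change; a 1.0 cm sex difference in BATT; correlation 0.3 between baseline BATT and baseline PROMIS; residual SD of change s = 0.6 cm; modest effects of age (0.2 points per year) and sex (1 point) on 13-week PROMIS. Let k be the fraction of starting BATT lost and g the effect of starting BATT on 13-week PROMIS beyond baseline PROMIS, in points per cm.

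Large-sample fits (400,000 records, no measurement error) gave these slopes:

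| k | g | Model 3 type (change + baseline PROMIS) | Model 2 type (+ age, sex) | + age, sex, baseline BATT |
|---|---|---|---|---|
| 0 | 0 to 2 | 3.0 | 3.0 | 3.0 |
| 0.1 | 0 / 1 / 2 | 2.9 / 2.6 / 2.3 | 3.0 / 2.8 / 2.5 | 3.0 |
| 0.2 | 0 / 1 / 2 | 2.8 / 2.3 / 1.7 | 3.0 / 2.6 / 2.1 | 3.0 |
| 0.3 | 0 / 1 / 2 | 2.8 / 2.0 / 1.3 | 3.0 / 2.4 / 1.8 | 3.0 |

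Hand check. Ignoring baseline PROMIS, omitting starting BATT shifts the slope by −g·k·Var(B)/(k²·Var(B) + s²). With k = 0.2, Var(B) = 1.1² = 1.21 and s = 0.6, this is −g × 0.242/(0.0484 + 0.36) = −0.59g. The table gives (1.70 − 2.84)/2 = −0.57 per unit of g. The two agree; baseline PROMIS absorbs only a little here.

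Measurement error creates the same link even when true loss is unrelated to size. The article puts reliability above 0.9 (Quadriceps ultrasound). Taking 0.9, the error variance is 0.1 × 1.21 = 0.121. The correlation of observed change with observed baseline is then −0.121/(1.1 × √(s² + 0.242)), which is −0.19 at s = 0.3 and −0.14 at s = 0.6. The Model 3-type slope is 3s²/(s² + 0.242), about 0.8 and 1.8 respectively. If starting BATT is worth 1.5 to 3 points per cm, adding it raises these to 1.3–1.8 and 2.1–2.4. The remaining shortfall from 3 is ordinary attenuation, which adjustment does not repair.

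Strong assumptions (reliability 0.9, loss 10–21% of baseline, s = 0.3, 1.5–3 points per cm) give −0.7 to +0.5 for Model 3, −0.4 to +0.6 with sex added, and +1.2 to +1.8 with sex and baseline BATT. With s = 0.6 the Model 3 slope is 0.9–1.6, against 2.1–2.4 with baseline added. If starting BATT acts only through baseline PROMIS (s = 0.4 to 0.6), Model 3 and the fully adjusted model both give 1.2–1.9, so the omission costs almost nothing.

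**3. What a single cohort can carry**

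The plan works with 45 evaluable patients per cohort; a 25% loss from 56 leaves 56 × 0.75 = 42. Model 3 has 4 predictors (baseline PROMIS and three changes).

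- As written: 42/4 = 10.5 to 45/4 = 11.3 patients per predictor.
- With age and gender (6 predictors): 42/6 = 7.0 to 45/6 = 7.5.
- With three baseline values as well (9 predictors): 42/9 = 4.7 to 45/9 = 5.0.

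**The case against.** The case against has several parts.

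- **The bias is not shown.** A reader might infer from the sex-specific cut-offs that larger patients lose more and that the association is therefore biased. The documents do not support that. The cut-offs rest on healthy young adults and show a difference in size, not in loss or recovery. Nothing in the article says that starting muscle predicts 13-week PROMIS once baseline PROMIS is in the model. This stands, and the point is therefore conditional.
- **Sign reversal is a corner case.** It appears only with a large proportional loss, little other variation in change and a strong direct effect of starting BATT. This stands.
- **Gender alone moves little.** Under the strong assumptions, adding sex shifts the slope only from −0.7/+0.5 to −0.4/+0.6. This stands. The starting values matter more than the demographics.
- **Model 1 also lacks baseline PROMIS.** A reader might count this as a fault, but the article labels that model unadjusted and Model 2 supplies the adjustment. It is no defect.
- **Sparse data justify a lean model.** About 5 patients per predictor is too few for the full set in one cohort. This stands against a nine-predictor single-cohort model, but not against two extra terms or a pooled fit.
- **The covariate list may be completed elsewhere.** The demographics are given as examples, and a separate analysis plan may exist. This carries less weight, because the article names demographics for one model and leaves them out of the next. That is a stated specification and not simple brevity.

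**Conclusion.** The point holds in conditional form. As specified, the ranking model omits the age and gender adjustment that Model 2 has, and no model accounts for starting muscle or strength. Confounding of the Model 3 coefficients needs two things: change related to starting size (through true loss or measurement error), and starting muscle, age or sex predicting 13-week PROMIS beyond baseline PROMIS. If both hold, the likely direction is towards zero. The size runs from none to most of the slope: 3.0 down to 1.3 on a true 3.0 in the main grid, a loss of (3.0 − 1.3)/3.0 = 57%, and further only under strong assumptions.

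Only BATT was simulated. That the ranking across BATT, grip and gait speed could shift follows by reasoning and was not calculated. It would go too far to say that the planned association is biased, or that its sign will reverse.

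**What to change.** 1. Name age and gender in Model 3, as in Model 2. This costs about two degrees of freedom per single-cohort fit.
2. Add the baseline values of the muscle measures to Model 3 in the pooled analysis that the article already plans as secondary, with a cohort term. In single cohorts, use this fuller model only as a sensitivity analysis.
3. Leave gait speed change and its baseline out for the emergency surgery cohort. A reader might assume that every covariate is already collected, but the Physical performance section and Table 1 show no gait speed at recruitment there. This implies two pooled fits:
   - BATT and grip in all three cohorts: 9 predictors (baseline PROMIS, two changes, two baselines, age, gender, two cohort indicators) on 126 to 135 patients, or 14 to 15 per predictor.
   - All three measures in the elective and medical cohorts: 10 predictors (baseline PROMIS, three changes, three baselines, age, gender, one cohort indicator) on 84 to 90 patients, or 8.4 to 9.0 per predictor.
4. Leave Model 1 as the crude model.

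The change is to analysis wording only and needs no new data. It should be settled before any results are seen, including those of the planned interim analysis. The downside is the degrees of freedom used, and the baseline terms will not remove attenuation due to measurement error.

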### Acute sarcopenia

Sarcopenia will be defined as per EWGSOP2 as handgrip strength below 16 kg in women or below 27 kg in men [2, 55], in combination with low muscle quantity or quality. Cut-offs for low muscle quantity and quality will be evaluated comparing the cohort against reference data in healthy young adults; cut-offs for BATT of 3.85 cm in women and 5.44 cm in men have been proposed [11]. Severe sarcopenia will be defined as additional presence of low physical performance; gait speed 0.8 m/s or less [56] or SPPB of 8 or less [57]. Acute sarcopenia will be defined as incident sarcopenia compared to baseline measurements at recruitment. The prevalence of sarcopenia will be calculated at each visit.

### Patient and public involvement

Older adults have been involved in the design and development of this research. We will host further discussion groups when analysing the results (interim and final). This will be particularly valuable when determining the significance of unexpected results. The interim meeting will be of potential value in assessing if any protocol amendments are necessary. The third discussion group will also be used to co-produce the study report. The findings of this research will be disseminated to all participants and their advocates through a written summary. The participants who are enrolled in this study itself will be the best placed to assess and comment on the acceptability of the procedures used during this study. Within the study design itself, we have devised a questionnaire to derive a multi-faceted acceptability score for assessment of muscle quantity using ultrasound, handgrip strength, and walking speed. We consider that formally interviewing participants could lead to unnecessary burden, given the time they will have already dedicated to the study itself. However, any informal feedback given will be recorded to guide further research and healthcare policy. The final formal meeting that is planned with our discussion group will encompass a full evaluation of the importance of the results of this study and will be used to co-produce any protocols for future research, as well as recommendations for healthcare policy.

### Trial registration

This study was registered on ClinicalTrials.gov (identifier: NCT03858192) on 28th February 2019.

## Discussion

This study will fully characterise changes in muscle quantity and function in a clinical setting and will provide invaluable information to researchers, clinicians, and patients. The results of this study have potential to lead on directly to further interventional studies to counteract these changes, with particular focus on identified mechanistic associations and clinical factors to guide risk stratification. The results may also lead to direct changes in clinical practice, including the embedding of our research tools into clinical practice, and changes in policy, such as promoting early mobilisation. Providing patients and members of the public with increased knowledge on their risk of declines in muscle quantity and function, and what this is likely to mean for them, can help to empower them in their own decision making and engagement with treatment and therapy.

We recognise that there are a number of limitations of our study. Firstly, this is a single site study, and therefore, the results may not be generalisable to the wider population. Secondly, the cohorts we have included are disease-specific. However, we consider that our results will provide proof of concept, which can be used to guide further research to increase understanding in other disease populations. As described, our study has been powered to detect within group differences in the minimally clinical important differences as derived from other studies. However, this has not been powered separately for gender and other covariates (e.g. cancer vs. not), which may affect measurements. Interim analysis has been planned and our patient and public involvement panel will be involved in the interpretation of these results. At this stage, we will review the overall progress of the study and consider if protocol amendments may be necessary.

There is some evidence that position can affect measurement of muscle quantity by ultrasound and BIA [58, 59]. However, the results will be compared to a reference group of young healthy individuals taken in the same position as we have described, using the same technique [11]. The position described is one that we can consider to be feasible for measurements in a variety of different clinical environments, whilst ensuring the quadriceps are relaxed. Particular care will be taken to standardise the position of each measure for each participant across separate visits. Nevertheless, we acknowledge that due to measurements being taken in different clinical environment, there may be small uncontrollable differences in position across visits.

Venepuncture and physical activity recording have both been included as optional aspects of the study, and it is not known what percentage of participants will agree to these. However, venepuncture was previously included as an optional aspect within our pilot study and all participants were in agreement with this [24]. We recognise that there will be limitations of physical activity measurements recorded through the Fitbit Inspire. These devices will be unable to specifically measure change in position (e.g. sit to stand). Previous studies using raw accelerometer data have shown a floor effect when measuring physical activity in frail, sedentary older adults [60]. However, physical activity measures using Fitbits have also shown to correlate well with raw accelerometer data in studies involving older adults [61]. The Fitbit Inspire is considered to be an acceptable device for older adults due to its simple wristwatch-like design, and their low cost means that they are potentially utilisable in clinical practice. Within our study, we will assess the feasibility of using these devices and assess the validity of data recorded as covariates and predictors of change in muscle parameters and physical function.

Despite these limitations, we consider the recruitment of a complex heterogeneous population to be a strength of this study. Frail older adults are frequently under-represented in research studies. It is not possible to be certain that changes seen in young healthy adults are concordant with changes in older adults. Determining the mechanisms involved in the development of acute sarcopenia will enable risk stratification, and targeted interventions to prevent or even reverse the effects.

## Data Availability

Anonymised data will be available from the corresponding author upon reasonable request.

## Abbreviations

ADLs: Activities of Daily Living
CFS: Clinical Frailty Scale
cm: Centimetres
DHEA-s: Dehydroepiandrosterone sulfate
FI: Frailty Index
hsCRP: High sensitivity C-Reactive Protein
IGF-1: Insulin-like Growth Factor 1
IL-6: Interleukin 6
kg: Kilograms
L3: Third Lumbar vertebra
MNA: Mini-Nutritional Assessment
PROMIS: Patient Reported Outcome Measures Information System
SD: Standard Deviation
SPPB: Short Physical Performance Battery
TNF-α: Tumour Necrosis Factor Alpha
TPA: Total Psoas Area
